# Design and rationale of the non-interventional, edoxaban treatment in routiNe clinical prActice in patients with venous ThromboEmbolism in Europe (ETNA-VTE-Europe) study

**DOI:** 10.1186/s12959-018-0163-7

**Published:** 2018-05-01

**Keywords:** Venous thromboembolism (VTE), Edoxaban, Direct oral anticoagulant (DOAC/NOAC), Anticoagulation, Registry

## Abstract

**Background:**

Venous thromboembolism (VTE, including deep vein thrombosis [DVT] and pulmonary embolism [PE]) has an annual incidence rate of 104–183 per 100,000 person-years. After a VTE episode, the two-year recurrence rate is about 17%. Consequently, effective and safe anticoagulation is paramount. Edoxaban is a direct oral anticoagulant (DOAC) approved VTE treatment. Current safety and efficacy data are derived from clinical trials, and information about treatment durations beyond 12 months are not available.

**Methods:**

ETNA-VTE-Europe is an 18-month prospective, single-arm, non-interventional, multinational post-authorisation safety study. Approximately 310 sites across eight European countries (Austria, Belgium, Germany, Ireland, Italy, the Netherlands, Switzerland and the United Kingdom) will participate in the study, with the intention to represent the regional distributions of centres, healthcare settings and specialties. An estimated cohort of 2700 patients will be recruited, the only enrolment criteria being acute symptomatic VTE, no participation in an interventional study, and treating physician decision to prescribe edoxaban independently from the registry. Data from patient medical records and/or telephone interviews will be collected at baseline, 1, 3, 6, 12 and 18 months. The primary objective is to evaluate the 18-month rate of symptomatic VTE recurrence in patients with VTE treated with edoxaban outside a clinical trial. The co-primary objective is to evaluate the real-world rates of bleeding and adverse drug reactions. Secondary outcomes include rates of other patient-relevant safety events, adherence to and discontinuation of edoxaban. Furthermore, 12-month ETNA-VTE-Europe data will be considered in the context of those for patients receiving different anticoagulants in the PREFER in VTE registry and Hokusai-VTE clinical trial.

**Conclusions:**

ETNA-VTE-Europe will allow the safety and effectiveness of edoxaban to be evaluated over an extended period in acute symptomatic VTE patients encountered in routine clinical practice. Findings will be informative for European practitioners prescribing edoxaban as part of real-world VTE treatment/prevention.

**Trial registration:**

ClinicalTrials.gov Identifier: NCT02943993.

## Background

Venous thromboembolism (VTE), which encompasses both deep-vein thrombosis (DVT) and pulmonary embolism (PE), has an annual incidence rate of approximately 104–183 per 100,000 person-years in individuals of European descent [1]. VTE is the third most common cardiovascular disease. The case-fatality rate is higher after PE than after DVT [2, 3]. Nevertheless, both events increase the probability of subsequent recurrent VTE, which affects approximately 17% of patients at 2 years, indicating that VTE is a chronic disease [4]. Consequently, effective anticoagulation to treat first-time VTE and prevent its recurrence is paramount.

Edoxaban is a direct oral anticoagulant (DOAC), which exerts its effects through inhibition of factor Xa. Based on results from the ENGAGE AF-TIMI 48 and Hokusai-VTE trials [5, 6], it was approved by the European Medicines Agency (EMA) regulatory for two main indications: the prevention of stroke/systemic embolism in patients with non-valvular atrial fibrillation (NVAF) with one or more risk factor, and the treatment/secondary prevention of acute VTE (DVT and/or PE) in adults [7]. However, current evidence for the safety and efficacy of edoxaban is derived from the patient populations enrolled in clinical trials. Furthermore, though current guidelines recommend that anticoagulation following VTE should be continued for at least 3 months and up to an indefinite duration, depending upon the risk of recurrence [8], no data currently exist for treatment with edoxaban beyond 12 months.

As part of an ongoing European risk-management plan, several post-authorisation safety studies (PASS) have been designed to assess the real-world outcomes of edoxaban-treated patients in the EMA-approved indications [9]. Here we describe the design and rationale for the “Edoxaban Treatment in routine cliNical prActice for patients with acute Venous ThromboEmbolism in Europe” (ETNA-VTE-Europe) PASS, the protocol for which has been reviewed and approved by the EMA’s Pharmacovigilance Risk Assessment Committee (PRAC), in accordance with new regulatory requirements. The aim of this PASS is to gain further insight into the safety and effectiveness of treatment and secondary prevention of VTE with edoxaban up to 18 months in routine clinical practice. This study forms part of a global program and safety data will eventually be pooled with ETNA-AF-Europe data and with those from similar Japanese, Thai, Chinese, Taiwanese and Korean regional registries to assess the safety outcomes associated with edoxaban on a worldwide scale.

## Methods

ETNA-VTE-Europe is a single-arm, multinational, prospective, non-interventional PASS, which will be conducted across approximately 310 sites in 8 European countries (Austria, Belgium, Germany, Ireland, Italy, the Netherlands, Switzerland and the United Kingdom). The registry will enrol approximately 2700 patients with acute VTE treated with edoxaban, who will be followed over the 18 months subsequent to the index VTE. Approval from the responsible ethics committees and institutional review boards will be obtained prior to protocol implementation. Informed consent will be obtained from all patients prior to enrolment and compliance with the Declaration of Helsinki will be ensured throughout the study.

### Objectives and outcome measures

The primary objective of ETNA-VTE-Europe is to quantify the long-term rate of VTE recurrence in a large, real-world population of acute symptomatic VTE patients prescribed edoxaban as part of their initial treatment regimen. Accordingly, the primary outcome measure will be the proportion of such patients who experience recurrent symptomatic VTE on one or more occasions within the 18 months following their index VTE, regardless of the length of edoxaban exposure.

The co-primary objective is to collect and evaluate real-world safety data regarding adverse drug reactions (ADRs) in patients treated with edoxaban across the currently approved indications. Therefore, ETNA-VTE-Europe data will be combined with 18-month safety data from the Edoxaban Treatment in routine cliNical PrActice for patients with non-valvular Atrial Fibrillation in Europe (ETNA-AF-Europe) study, a parallel European PASS evaluating the safety and effectiveness of edoxaban in real-world treatment of atrial fibrillation (AF) [10]. The outcome measure will be the proportion of patients who experience death (all-cause, cardiovascular, and VTE-related), bleeding events (major, clinically relevant non-major [CRNM], and minor bleeding; defined according to International Society on Thrombosis and Haemostasis [ISTH] criteria [11]), hepatic events, and/or other ADRs before the 18 month time-point in the two studies.

Secondary objectives are as follows: to evaluate the effects of persistent edoxaban use and permanent discontinuation on the rate of recurrent symptomatic VTE; to assess the rates of patient-relevant safety outcomes, including bleeding, ischaemic/haemorrhagic stroke, systemic embolic events (SEE), post-thrombotic syndrome (PTS), death, and hospitalisation due to cardiovascular causes; and to characterise the extent of adherence to edoxaban, reasons for and rate of discontinuation. To evaluate the effectiveness and safety of edoxaban relative to other anticoagulants, primary and secondary ETNA-VTE outcome data will be appraised in the context of those from the PREFER in VTE real-world registry and Hokusai-VTE clinical trial [12, 13]. The influence of study setting will also be explored by considering real-world ETNA-VTE data in the context of edoxaban data from the Hokusai-VTE clinical trial [12].

### Site selection

In order to represent the regional distributions of centres, healthcare settings, specialties, and approaches to VTE treatment, a sequential site selection process is underway. This involves identification of potential sites, acquisition of relevant institutional details via a feasibility questionnaire, assessment of suitability, and invitation to participate. To be considered eligible, sites are required to have access to acute VTE patients expected to receive edoxaban treatment, the ability to access the Electronic Data Capture (EDC) system and record data in English, and adequate time and staff to perform all study-related documentation activities. They must also agree to complete a screening log with the aim of maximising the potential for consecutive enrolment, and to perform follow-ups according to routine clinical practice. There is an upper limit of 100 patients per site.

### Patient recruitment

The original version of the ETNA-VTE-Europe protocol was approved by the Swiss Agency for Therapeutic Products (Swissmedic) and the central Ethics Committee in Switzerland in February 2015. Accordingly, Swiss sites began enrolling patients at this time. However, protocol revision was necessary due to a change in EMA legislation and a revised PRAC process in July 2015. Upon the approval of the new protocol by the EMA’s PRAC in September 2016, Swiss regulatory bodies were informed of the changes and new approval sought. Patient recruitment according to the revised protocol is now underway, taking place in two waves; the first extends from the last quarter of 2016 to the second quarter of 2018 (Switzerland and Germany) and the second from the first quarter of 2017 to the last quarter of 2018 (all other countries). In each country, the recruitment period will last 2 years, with the aim of obtaining a representative study population of approximately 2700 VTE patients from a variety of healthcare settings.

To be included in the study, patients must have been diagnosed with initial or recurrent acute VTE (distal or proximal DVT and/or PE) that occurred no more than 2 weeks prior to enrolment. In addition, the treating physician must have decided to prescribe the patient edoxaban, with indications that are in line with the edoxaban Summary of Product Characteristics (SmPC). All treatment decisions are independent of the registry and completely at the discretion of the treating physician and/or patient, with no reimbursement for any drugs or therapy received during the study. As such, any concomitant treatment is allowed and changes to medication are unrestricted. The only exclusion criteria are lack of written informed consent and participation in a simultaneous interventional study.

### Documentation and assessment

Data for this study will be sourced from medical records and, when in line with routine clinical practice, from telephone calls between the patient and treating physician. As a non-interventional study, no patient contact, examinations, laboratory tests or procedures are compulsory, and will only be carried out at the discretion of the treating physician, as and when deemed appropriate and without registry influence. A standardised electronic case report form (eCRF) will be completed by the site shortly after enrolment and again after every interaction with a patient over the subsequent 18 months. The eCRFs will be uploaded to the secure, internet-based Medidata Rave EDC system.

Given that the edoxaban SmPC recommends 5 days of parenteral anticoagulation following VTE before starting edoxaban treatment [7], baseline is defined as the first day of heparin/fondaparinux administration after the index acute VTE event. The first data entry, which will be completed following enrolment and within 2 weeks of the index VTE, will include details of baseline patient characteristics, comorbidities, VTE-related parameters, past and current therapy, and other relevant assessments made according to site protocol (Table 1). Memory aids will be provided to all patients at enrolment, with space to record edoxaban-related treatment changes, use of concomitant medication, adverse events, hospitalisation, physician contact, and productivity loss. This aid can be used to assist with recall during subsequent visits/telephone calls, but are voluntary and will not be formally assessed. In each country, all patients will be followed until the last patient for that particular country has completed the 18-month documentation period, in line with EMA requirements. At this point, a last-patient-out (LPO) questionnaire, requesting a minimum of vital status, will be issued for each patient enrolled in the respective country.

**Table 1 Tab1:** Time points for data assessment

	Baseline*	1 month	3 months	6 months	12 months	18 months	Country-specific LPO
Eligibility criteria^(1)^	X						
Baseline characteristics^(2)^	X						
VTE-related parameters^(3)^	X	X^§^	X^§^	X^§^	X^§^	X^§^	
Edoxaban therapy^(4)^	X	X	X	X	X	X	
Concomitant anticoagulants	X	X	X	X	X	X	
Interventions	X	X	X	X	X	X	
Adherence to VTE therapy^(5)^	X	X	X	X	X	X	
Recurrent VTE^(6)^		X	X	X	X	X	X^†^
Other clinical events^(7)^	X	X	X	X	X	X	
Hospitalisation for cardiovascular disease^(8)^		X	X	X	X	X	
PTS^(9)^	X		X		X	X	
Vital signs^(10)^	X	X	X	X	X	X	
Laboratory parameters^(9)^	X	X	X	X	X	X	
ADRs^(11)^	X	X	X	X	X	X	

*Legend:* VTE, venous thromboembolism; PTS, post-thrombotic syndrome; ADR, adverse drug reaction; LPO, last patient out. ^(1)^ Confirmed first or recurrent VTE within the 2 weeks preceding enrolment; treated with edoxaban according to Summary of Product Characteristics; written informed consent; no simultaneous interventional study participation. ^(2)^ Age and gender, alcohol consumption, smoking status, frailty, comorbidities, and medical history. ^(3)^ Details of past and current VTE risk factors, symptoms, diagnosis, interventions, treatment, and related clinical events (stroke, bleeding events, systemic embolism, non-valvular atrial fibrillation, and malignancies). ^(4)^ History and current status, including dose, prescription intervals, and any changes to edoxaban treatment since last data point (including permanent discontinuation, in which case date, reason and subsequent therapy must be provided). ^(5)^ Physician judgment only. ^(6)^ Timing, diagnosis and interventions. ^(7)^I.e. death, stroke, bleeding events, systemic embolism, non-valvular atrial fibrillation, and malignancies. ^(8)^ Admittance and discharge dates, clinical event, and use of the emergency room and/or intensive care unit. ^(9)^ If assessed. ^(10)^ Including blood pressure, heart rate, height and weight. ^(11)^ As per the Guideline on Good Pharmacovigilance Practices (GVP) Module VI (Management and reporting of adverse reactions to medicinal products; EMA/873138/2011 Rev. 1) [16]; coding according to the standardised Medical Dictionary for Regulatory Activities (MedDRA).*Defined as the first day of heparin administration after the index acute VTE event. ^†^Since 18-month time point. ^§^Changes in symptoms/diagnosis and any other VTE-relevant information

Upon completion of the ETNA-VTE-Europe registry, data will be extracted for the following time points: baseline, 1, 3, 6, 12 and 18 months. Details of the parameters to be evaluated at each time point are outlined in Table 1. The current status, change/events since baseline and change/events since the previous time point will be assessed for each parameter, as appropriate. In addition, recurrence of symptomatic VTE and death since the 18-month time point will be retrospectively documented at the time of LPO per country.

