### Quality control

ETNA-VTE-Europe will be conducted in accordance with the Guidelines for Good Pharmacoepidemiology Practice (GPP) and the EMA Guideline on Good Pharmacovigilance Practices (GVP) Module VIII (management and reporting of adverse reactions to medicinal products; EMA/813938/2011 rev 1) [16, 17]. Automated checks for plausibility and integrity will be carried out at data entry to permit correction or confirmation by the site. Furthermore, approximately 30% of sites will be randomly selected to undergo on-site monitoring, during which random source data verification will be performed. In particular, monitoring activities will closely assess the completeness and correctness of safety data. Patients with missing observations for a particular time point and/or parameter will be omitted from the corresponding analyses.

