### Sample size calculations

Assuming an overall 18-month symptomatic VTE recurrence rate [12, 13] of 8.0% in patients who receive edoxaban (regardless of treatment discontinuation) and a relative precision of 15% for a two-sided 95% confidence interval (95% CI), data for 1964 patients will be required to assess with sufficient accuracy the primary outcome. Given an expected dropout rate of 25%, enrolment of 2700 patients should result in an adequate sample size for evaluation at 18 months.

In order to obtain a dataset as large as possible for co-primary outcome assessment, safety data from ETNA-VTE-Europe will be combined with 18-month safety data from ETNA-AF-Europe, a sister European PASS study of edoxaban in approximately 13,100 patients with NVAF [10]. Together, these studies will enrol approximately 15,800 patients, with an overall expected 18-month dropout rate of 20%. Consequently, data for approximately 12,640 patients should be available at 18 months to assess the incidence rates of interest and their 95% CIs. A key aim of this combined analysis is to provide sufficient statistical power to capture uncommon ADRs with low incidence rates; for those that occur at rates of 0.1–1.0%, the corresponding precision of 95% CIs will range from ±0.06% to 0.17%.

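### For recurrent VTE, the last-patient-out questionnaire looks back only to month 18, so patients with no month-18 record keep an unfilled gap inside the primary-outcome window

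*Protocol article*

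**What the plan says.** All references are to the protocol article.

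- **Primary outcome** (Objectives and outcome measures), measured as the share of the cohort to which this applies: "experience recurrent symptomatic VTE on one or more occasions within the 18 months following their index VTE, regardless of the length of edoxaban exposure". Stopping edoxaban does not take a patient out of this outcome.
- **Who is covered at country close** (Documentation and assessment): "a last-patient-out (LPO) questionnaire, requesting a minimum of vital status, will be issued for each patient enrolled in the respective country".
- **Look-back at LPO** (same section): "recurrence of symptomatic VTE and death since the 18-month time point will be retrospectively documented at the time of LPO per country". In Table 1 the LPO cell for recurrent VTE carries a dagger, explained as "Since 18-month time point". Text and table agree on recurrence.
- **Contact during follow-up** (same section): "no patient contact, examinations, laboratory tests or procedures are compulsory".
- **Look-back at scheduled time points** (same section): events are assessed both from baseline and from the previous time point.
- **Missing data** (Quality control): "Patients with missing observations for a particular time point and/or parameter will be omitted from the corresponding analyses".
- **Expected loss** (Sample size calculations): "Given an expected dropout rate of 25%, enrolment of 2700 patients should result in an adequate sample size for evaluation at 18 months".

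**The concern.** Take a patient whose last documented contact is at month 6 and for whom no month-18 record is ever completed. The LPO questionnaire is issued for this patient, but its recurrence item starts at month 18. Months 6 to 18, which belong to the primary outcome, are never asked about, while the time after month 18, which does not, is.

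An analysis plan cannot repair this later, because events that no form asks about cannot be analysed. Kaplan-Meier analysis, foreseen where applicable, would use the patient's time up to month 6 and censor there. It would not recover a later event, and it relies on the censoring being uninformative. If patients who drop out of routine documentation recur more or less often than those who stay, the 18-month proportion is biased, although a form is already planned that could narrow the gap.

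**Working it through.** **1. The plan's own sample size.** Inputs from Sample size calculations: rate p = 0.08, relative precision 15% (half-width 0.15 × 0.08 = 0.012), two-sided 95% CI, dropout 25%, enrolment 2700.

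- n = 1.96² × p(1 − p) / 0.012² = 3.8415 × 0.0736 / 0.000144 = 1963.4, rounded up to 1964. The stated figure is reproduced.
- Enrolment needed: 1964 / 0.75 = 2619. The planned 2700 covers it.
- Expected evaluable: 2700 × 0.75 = 2025. Half-width at 8%: 1.96 × √(0.0736 / 2025) = 0.0118, or 1.18 points (14.8% relative).

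The planned precision is therefore met without recovering anyone.

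**2. Who falls into the gap.**

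| Patient | Is the time up to month 18 covered? |
|---|---|
| Month-18 record present, earlier visits missed | Yes, through the look-back to baseline and to the previous time point |
| No month-18 record, recurrence already recorded | At least one event is already known |
| No month-18 record, no recurrence recorded | No: last contact to month 18 is not covered by any stated instrument |

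Only the third row is the problem. Its upper limit is 2700 × 0.25 = 675 patients.

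**3. How large the bias could be.** The article gives no recurrence rate for patients lost, so this is an illustration. Let completers recur at 8% and lost patients at rate q.

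- Full-cohort rate = 0.75 × 8% + 0.25 × q.
- Error of the completers-only estimate = 8% − full-cohort rate = 0.25 × (8% − q).

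| Assumed q | Full-cohort rate | Error, points |
|---|---|---|
| 4% | 7% | +1 |
| 8% | 8% | 0 |
| 12% | 9% | −1 |
| 16% | 10% | −2 |

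The error equals the planned half-width when 0.25 × |8 − q| = 1.2, so q = 8 ± 4.8, which is 12.8% or 3.2%. The logical limits for the full cohort are 162/2700 = 6.0% (none of the 675 recur) and (162 + 675)/2700 = 31.0% (all recur), where 162 = 0.08 × 2025.

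**4. What a wider look-back could do.** Assume, only to show the mechanism, that half of the 675 are recovered at random and q = 12%. The estimate becomes (162 + 0.12 × 337.5) / (2025 + 337.5) = 202.5 / 2362.5 = 8.57% against 9%. The error shrinks from 1 point to 0.43. The half-width moves only from 1.18 to 1.09 points.

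**5. Death.** One sentence asks for at least vital status for every enrolled patient and sets no start date. The later sentence limits death to the time since month 18. The Table 1 row that contains death has no LPO mark at all. The three do not match.

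**The case against.** The strongest case against the point has five parts.

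- **Deaths are not lost.** A reader might infer that early-lost patients have a gap for death as large as that for recurrence. The article does not support this: vital status at LPO shows whether such a patient has died, whenever that happened. What remains is the inconsistent wording and the date of death. This objection stands.
- **Precision is not at risk.** A reader might infer that the dropouts endanger the sample size. They do not, since 2025 exceeds 1964. This also stands.
- **The questionnaire may not be a patient contact.** It is issued for each patient, the data sources are medical records and routine telephone calls, and no contact is compulsory. A site that can still reach the patient or the records could have completed month 18, and one that cannot will recover little. This limits the yield. It does not justify starting the question at month 18 for those who can be reached.
- **Late ascertainment is weaker.** Recruitment lasts 2 years per country and LPO follows the last patient's month 18, so the first patients enrolled could be asked up to 24 + 18 = 42 months after the index event. Recovered recurrences would be ascertained differently from those of completers, and adjudication may lack material. This is a real cost. But the form already asks such a patient about months 18 to 42, so the change lengthens the look-back (in the month-6 example from 24 to 36 months) and does not create it.
- **LPO is meant to extend follow-up, and the full protocol may say more.** The article ties LPO to regulatory requirements and does not present it as a rescue tool. However, the point rests on a look-back that the article states twice, not on a missing detail.

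**Conclusion.** The point holds for recurrent VTE in patients who have no month-18 record and no recurrence already recorded. Followed as written, the plan leaves the interval from last documented contact to month 18 uncovered and omits these patients from the 18-month proportion. For death, the finding is only that the window is worded inconsistently and that the date should be recorded.

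Up to 675 patients (25%) are affected. The number is lower where a recurrence is already known, and fewer still can be recovered where consent was withdrawn or records are out of reach. The direction and size of the bias are unknown. The 12.8% and 3.2% thresholds rest on an assumed 8% in completers and on all 675 being without outcome. A reader might go further and conclude that lost patients have a particular excess risk, or that a given share would be recovered. The article gives no figure for either, so no specific bias or gain can be claimed. The benefit is less potential attrition bias and more complete data. It is a worthwhile improvement to an existing form, not the correction of a sample-size error.

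**What to change.** For patients without a month-18 record, start the LPO look-back for recurrence and death at the last documented contact, completed from medical records or patient contact, and record the date of each recurrence and of death. Align the two sentences on LPO and Table 1, so that vital status and its window are stated once and consistently.

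Send recovered recurrences dated up to month 18 to the clinical events committee like any other, and include them in the primary analysis. Add a sensitivity analysis that excludes LPO-recovered data, and report how many patients remain without month-18 information.

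The cost is longer recall, later and different ascertainment for these patients, and a minor amendment of protocol and eCRF. The latter may need regulatory notification, since the protocol was approved by the EMA's safety committee. Changing the form before the first country reaches LPO avoids having two versions in use.
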